patients prescribed statins stop taking them. Reducing CVD-related morbidity, mortality and health care costs will depend to a great degree on effective strategies to help patients improve medication adherence and other health behaviors. Financial incentives have been shown to be effective at improving patient health behaviors including medication adherence in a wide variety of contexts. The delivery of such incentives has been enhanced by the recent development of new wireless technologies that facilitate the measurement of daily medication adherence and the provision of incentives in an automated fashion. However, the relative effectiveness of incentives based on process (e.g. medication adherence) vs. outcome (e.g. improvements in LDL cholesterol) is unknown. Traditional economists would argue that incentivizing outcomes is likely to be more effective (each individual determines the most efficient path to a desired result) whereas behavioral economists would argue for incentivizing on process (which may be simpler, more tangible, and provides more frequent feedback). A rigorous experimental study that examines the relative effectiveness of equivalent value incentives based on process (statin adherence), outcomes (LDL cholesterol), or a combination of process and outcomes would provide an answer to a question of fundamental importance to the design of incentive programs. The results will grow in policy relevance with the implementation of Section 2705 of the Affordable Care Act in 2014, which allows employers to utilize as much as 30% (50% including smoking) of premiums for outcome-based incentives for metrics like LDL. A recent set of guidelines related to cholesterol management (Stone et. al, *Circulation* 2013) identified groups of patients at elevated risk of CVD that should be treated with statins but changed the orientation of clinical practice away from achieving particular LDL levels. The study DSMB determined that, since this study will enroll subjects at elevated risk for cardiovascular disease, it is reasonable to use changes in LDL as the primary outcome. . Improved adherence to statins will plausibly lead to reductions in LDL cholesterol; both improved statin adherence and lower LDL cholesterol could reduce CVD risk.

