### **Design**

This 4-arm RCT will compare the relative effectiveness and cost-effectiveness of process versus outcome-based financial incentives in improving LDL cholesterol in patients who are at high risk for CVD and have been prescribed statins. Adherence in all groups will be measured using an electronic pill container as a recording device. The intervention will consist of an active phase of 12 months followed by 6 additional months of observation. Participants will be randomized evenly into one of 4 arms. The primary outcome will be change in LDL cholesterol from baseline to 12 months. All participants will have LDL cholesterol checked at baseline, 3, 6, 9, and 12 months during the interventions, and at 18 months (without incentives, in order to assess the sustainability of the effects achieved by the incentives). We selected cholesterol for this study of process versus outcomes because a change in LDL depends on sustained adherence to a statin. LDL cholesterol is easily, inexpensively and objectively measured. The impressive degree of risk reduction associated with LDL lowering is well established. The interventions will consist of financial incentives lasting 12 months for arms 1, 3, and usual care (no incentives) for arm 4. The net value of incentive payments are equivalent in arms 1, 2 and 3. Participants in Process (arm #1) and the Process plus Outcomes (arm #3) groups will be eligible for an adherence-based sweepstakes. The expected value of the daily sweepstakes payments will be \$1.40 in the Process arm, and will be \$0.70 in the Process with Outcomes arm. Thus, participants in arms 1 and 3 may benefit from daily engagement and the opportunity for multiple, short-term rewards in changing adherence behavior. At months 3, 6, 9, and 12 every participant in the Outcomes (arm #2) and the Process with Outcomes (arm #3) interventions will be eligible for a payment (\$126 to arm #2; \$63 to arm #3) if the participants LDL has improved by 10 mg/dl compared to the LDL at the end of the previous quarter. The daily expected value of these rewards per day will be equivalent to each of the other intervention arms. Study sites. Participants in the study will be employees of corporations with CVS-Caremark pharmacy benefits (see letter of support from [name]) and Health System patients (Penn Medicine and Lancaster General Health (LGH)). The study will be run by UPENN investigators, who will communicate with participants through the Way to Health portal and by phone. Inclusion criteria. On further review of the recent AHA guidelines, we are changing our inclusion criteria to invite anyone with LDL190 (regardless of disease risk factors) as well as anyone with CAD with LDL100. The criteria includes: Individuals at high risk of a cardiac event, specifically one of the following: Individuals with clinical ASCVD (defined as diagnosis with myocardial infarction, stroke, or peripheral vascular disease) with an LDL greater than or equal to 100 mg/dl ; Individuals with Diabetes (between the ages of 40-75) with an LDL greater than or equal to 100 mg/dl; Individuals without clinical ASCVD or diabetes with LDLC with an LDL greater than or equal to 100 mg/dl and estimated 10-year ASCVD risk 7.5%; Individuals without clinical ASCVD or diabetes with LDL cholesterol 190 mg/dl A prescription filled for a statin medication within the last 12 months (derived from pharmacy records); Imperfect statin adherence level as defined by one of the following: Medication Possession Ratio (MPR) less than or equal to 80% A score 0 on the 8-item Morisky Medication Adherence Questionnaire completed during enrollment Exclusion criteria. Patients will be excluded if they 1) are younger than 18 years old; 2) have a contraindication to further statin use or have suffered statin side effects, such as myopathy; 3) will not or cannot give consent; 4) have a history of active or progressive liver disease are participating in another clinical trial with related aims, 6) have co-morbidities likely to lead to death within a short period (e.g. metastatic cancer), or 7) are prescribed by their doctor PCSK9 inhibitor injections coupled with statin therapy. Study Procedures Recruitment. All potentially eligible employees within the CVS-covered group will be contacted via existing communication channels through CVS. Potentially eligible employees will have evidence of diabetes medication use and/or CVD medication use in the CVS pharmacy database. These individuals will be sent letters (paper or email) describing the study and inviting them to enroll. Potentially eligible patients recruited from Penns Health system will be contacted by the study team via letter, email and phone calls. Baseline assessment

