
for participants. Interested employees/patients will have the option of entering data related to eligibility and their demographic and clinical characteristics through the Way to Health internet portal or by phone. The informed consent can be accessed on the study portal and signed electronically. The informed consent contains contact information for the study team if the participant wishes to go over the consent form with a team member by phone before electronically agreeing to participate by clicking the 'I want to participate' button at the end of the electronic consent form. If the patient agrees to complete the informed consent over the phone with the coordinator, the patient is allowing the coordinator to electronically agree to participate by clicking the 'I want to participate' button at the end of the electronic consent form. Each potential participant will visit a local participating laboratory (through the Quest national chain of commercial laboratories) to confirm that their LDL is greater than 100 mg/dl. Approximately 3mL of blood will be drawn at each visit. All laboratory procedures will be paid for by the study. The enrollment interview and baseline labs will allow investigators to determine final eligibility for the study. The Quest corporation has 24 hour appointment scheduling and 2,000 lab locations; these locations are in every state as well as Puerto Rico. If the participant is from Penn Medicine, the study coordinator will order their labs in EPIC so the lab can be completed at their doctor's office. Our group has agreements in place with the Quest chain allowing research participants nationwide to have phlebotomy (blood draws). In the context of generous participation incentives (as will be provided in this study), the requirement of providing biological specimens at local laboratories has not been a barrier to program implementation. In another ongoing study, we have used Quest to enable 500 participants to get labs drawn at local laboratories.

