LDL decreases at least 10 mg/dl in the 3 months since the last visit. Over a year, these payments will be equivalent in magnitude to those in the process arm. The 3-month payment for the Outcome arm (arm #2) will be \$126, while the payment for the Process with Outcomes Incentive arm (arm #3) will be half this value, or \$63. Notably, if a participant in the Outcomes arm or the Process plus Outcomes arm achieves a reduction in LDL 20 mg/dl during one quarter of the trial and that reduction persists during the next quarter, the participant would be eligible for the outcome incentive at the end of both quarters, even if no further reduction in LDL took place during the second quarter. For instance, if a patient in the Outcome arm had an LDL decrease from 150 to 130 mg/dl between baseline and month 3, and also had an LDL of 130 mg/dl at month 6, that person would receive the incentive payment at month 3 and month 6. Participants in the intervention arms will be informed if they fail to meet adherence or LDL goals, and thereby are not eligible for payments. Providing this feedback may also improve adherence by taking advantage of anticipated regret.

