#### **Key exclusion criteria**

Patients will be excluded if they 1) are under 18 years old; 2) have a contraindication to further statin use or have suffered statin side effects, such as myopathy; 3) will not or cannot give consent; 4) have a history of active or progressive liver disease or 5) are participating in another clinical trial with related aims, 6) have co-morbidities likely to lead to death within a short period (e.g. metastatic cancer), or 7) are prescribed by their doctor PCSK9 inhibitor injections coupled with statin therapy.

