**Cost effectiveness analysis.** Measurement of costs and cost effectiveness. For our initial analysis, we will take a payer perspective. We will complete a within-trial analysis comparing incremental costs and incremental change in LDL in each arm, compared with control, during the 12 months of the trial. As a secondary analysis, we will substitute a societal perspective, which will include costs to patients, such as transportation and the time the patient devotes to the intervention. For both these analyses, costs will include: (1) incentive payments to participants (excluding incentives specific to the research); (2) costs of lab tests for those interventions in which lab tests are necessary to decide whether the participant has earned an incentive payment; (3) operational costs of implementing the interventions, including staff time administering the incentives and the computer platform to deliver the incentives (the Way to Health platform used in this study or an alternative that might be used by an employer); and (4) costs of the adherence measurement device (the electronic pill bottle and fees for connecting to the computer platform). We will also include the drug costs associated with statin medication use when adherence improves. Following usual practice in cost-effectiveness analysis we will conduct sensitivity analyses to assess the impact of uncertainty about these data, e.g., the standard error of the estimate of effectiveness, and to explore variations that might occur across employers. For the societal perspective cost-effectiveness analysis, we will follow the recommendations of the Second Panel on Cost-Effectiveness in Health and Medicine to compute additional costs to patients related to participating in an incentives program, including medication side effects, and time spent on the intervention, including travel and waiting time (using data from American Time Use Survey); time will

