## 2.3 Adherence & Association with $\Delta_{LDL}$ at 12 months

- Descriptive analyses. Describe measured adherence via pill bottle openings by arm, gender, race, income, baseline LDL-c. Describe measured adherence for the 12-month intervention period by arm and during final 30 & final 60 days of the intervention, again by arm.
- Association between measured adherence and change in LDL-c at 12 months; association between measured adherence in each 30 day/quarterly interval preceding each lab visit.

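### The cost-effectiveness analysis counts all LDL change as effect but charges drug cost only for better statin adherence, so regimen changes that are commoner in the outcome-paid arms would go uncosted

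*Combined protocol and SAP*

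**What the plan says.** **How arms are paid.** The protocol's Design section pays arms 2 and 3 when a participant's "LDL decreases at least 10 mg/dl in the 3 months since the last visit". A carry-over rule pays a second quarter when a 20 mg/dl fall persists. No condition is set on how the fall is achieved. Arm 1 is paid only for daily statin taking. On size, the protocol says "Over a year, these payments will be equivalent in magnitude to those in the process arm".

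**Why outcomes might work.** The Background gives the economists' argument for paying on outcomes: "each individual determines the most efficient path to a desired result". The Design section says LDL was chosen "because a change in LDL depends on sustained adherence to a statin".

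**Other lipid drugs.** The only related rule excludes, at entry, people who "are prescribed by their doctor PCSK9 inhibitor injections coupled with statin therapy". Neither document prohibits, standardises or expressly allows a statin switch, a dose change or an added lipid drug after randomisation. The outcomes text mentions doctors lowering a statin dose, but only as a limitation of the Medication Possession Ratio (MPR).

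**Costs and effects.** The cost-effectiveness part of the Analysis Plan sets each arm's extra cost over control against its extra LDL change over 12 months. Its costs are incentives, laboratory tests, operations and the device, followed by: "We will also include the drug costs associated with statin medication use when adherence improves". The societal version adds patient time, travel and side effects. The SAP has no cost-effectiveness section, so this sentence is the operative rule on drug cost.

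**Explaining LDL change.** SAP 2.3 plans the "Association between measured adherence and change in LDL-c at 12 months". The SAP names no statin product, dose or concurrent lipid drug as a variable, even at baseline.

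**The concern.** The two sides of the cost-effectiveness ratio do not match. Every mg/dl counts as effect, whatever produced it. On the drug side, only statin use tied to better adherence counts as cost.

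The mismatch bears on the contrast the trial was built to study. Arm 1 is paid to use one route, adherence, and that route is costed. Arms 2 and 3 are paid on LDL itself, so a participant who asks the prescriber for a different regimen can also earn the payment. The drug cost of that second route appears nowhere.

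At stake is Aim 4, the cost-effectiveness of each intervention. The LDL decreases observed by arm also feed the long-term cardiac model, and the same model serves the employer return-on-investment analysis. Both are conditional on a significant primary result.

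SAP 2.3 would not reveal the problem. Pill-container openings show neither drug nor dose, so the plan as written would not show whether regimens changed differently by arm.

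**Working it through.** **1. The plan's own incentive figures (protocol, Design).**
- Sweepstakes: 0.01 × $50 + 0.18 × $5 = $1.40 a day; × 365 = $511. This reproduces the stated values.
- Outcome arm maximum: 4 × $126 = $504.
- Combined arm maximum: 4 × $63 + $0.70 × 365 = $252 + $255.50 = $507.50.

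The maxima lie within 1.4% of each other, so the stated equivalence of payments holds at the maximum. The $504 serves as a yardstick below.

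**2. The omitted term.** Let *s* be the excess share of outcome-arm participants, over control, whose lipid regimen changes; *c* the extra annual drug cost of such a change; and *E* the arm's LDL effect in mg/dl.
- Cost left out per participant = *s* × *c*
- Understatement of cost per mg/dl = *s* × *c* / *E*

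**3. Inputs.** *E* = 10 mg/dl is the difference the protocol was designed to detect between an intervention arm and control. The documents give neither *s* nor *c*. I **assume** *s* from 5% to 20% and *c* from $100 to $2,000 a year.

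| *s* | *c* | Omitted per participant | Share of $504 | Per mg/dl at *E* = 10 |
|---|---|---|---|---|
| 0 | any | $0 | 0% | $0 |
| 5% | $100 | $5 | 1.0% | $0.50 |
| 10% | $500 | $50 | 9.9% | $5 |
| 20% | $500 | $100 | 19.8% | $10 |
| 20% | $2,000 | $400 | 79.4% | $40 |

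With a smaller effect, *E* = 5 mg/dl, the extremes double to $1 and $80 per mg/dl.

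**4. Sign.** The bias follows the sign of *s*. If regimen changes are equally common in all arms, the uncosted amounts cancel in the difference from control. If they are commoner in control, the outcome arms' incremental cost is overstated.

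**5. The primary analysis.** SAP 2.1 models LDL change on arm, baseline LDL and population. It uses neither adherence nor cost, so nothing above changes that contrast.

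**The case against.** **Crediting the LDL gain is legitimate.** An outcome incentive is meant to leave the route open, so LDL lowered through a new prescription is part of its intention-to-treat effect. This stands in full. The complaint is only that the cost of obtaining that effect is missing.

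**A bias towards the outcome arms is not shown.** A reader might infer that the rule favours arms 2 and 3. The documents do not support that: they give no rates of regimen change by arm. Nor does laboratory ordering help. For Penn Medicine participants "the study coordinator will order their labs in EPIC so the lab can be completed at their doctor's office", but this applies in every arm, so clinicians could act on LDL in control as well. What the payment scheme supplies is a reason why the rates might differ, since only arms 2 and 3 are paid on LDL.

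**Regimen changes are not expressly permitted.** Correct; the documents are silent. Not prohibited is enough for the costing gap to matter.

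**The adherence condition need not be one-sided.** A reader might take it participant by participant, so that improvements are charged and declines never credited. The sentence sits within a comparison of each arm with control, where the natural reading is at arm level. The device is mailed after assignment, so it offers no pre-randomisation baseline for a per-participant rule. I place no weight on that reading.

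**Existing provisions may cover it.** The planned sensitivity analyses vary uncertain inputs; they do not add a missing cost item. MPR for non-statin drugs is a secondary outcome, but it is aimed at spill-over, rests on CVS refill data and is not linked to cost.

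**It is a secondary economic analysis, and the amount may be negligible.** True at the low end of the assumed range. Without the tabulation, nobody can tell which end applies.

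**Conclusion.** The concern holds as a conditional point about the cost-effectiveness analysis. The drug-cost rule is narrower than the effect it is set against. If regimen changes are more frequent in arms 2 and 3 than in control, incremental cost per mg/dl is understated in those arms; with equal rates the bias is zero.

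The size rests wholly on assumed inputs: $5 to $400 per outcome-arm participant, against a maximum outcome payment of $504, or $0.50 to $40 per mg/dl at a 10 mg/dl effect. The direction cannot be established from the documents. The primary LDL result is untouched, and SAP 2.3 is incomplete as an explanation of LDL change rather than wrong. Because this is a stated costing rule that can give a wrong incremental cost for a named aim, and the remedy is cheap, it should be changed.

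**What to change.** **Protocol, Analysis Plan, cost-effectiveness analysis.** Replace the drug-cost sentence with:

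> Drug costs will include all lipid-lowering drugs (statin product and dose, and non-statin agents) for every participant in every arm over the 12 months, from EPIC or pharmacy records, whatever the direction of adherence change.

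**SAP 2.3.** Add a table of lipid-regimen changes from baseline by arm, shown beside adherence. Keep it descriptive. These are post-randomisation variables and should not enter the primary model as covariates.

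Neither change constrains prescribing.

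**Cost.** A prescription extract and two pieces of wording. The trial already queries EPIC to find Penn and Lancaster General patients, confirms statin fills from pharmacy records or the EHR, and collects medication data. Two limits should be stated: the SAP's spillover extract is from the Penn Medicine record only, so prescription data at Lancaster General need confirming; and prescriptions are not dispensed drugs. The outcome arms' cost ratios may look less favourable. If regimens prove balanced across arms, the table will show it.

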
## Objectives

### Overall objectives

The study will achieve the following Specific Aims: 1) Assess the effectiveness of a process-based incentive on lowering LDL cholesterol; 2) Assess the effectiveness of an outcome-based incentive on lowering LDL cholesterol; 3) Assess the effectiveness of a combined process plus outcomes incentive on lowering LDL cholesterol; 4) Assess the cost-effectiveness of each of the interventions.

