
#### **Key inclusion criteria**

Individuals at high risk of a cardiac event, specifically one of the following: Individuals with clinical ASCVD (defined as diagnosis with myocardial infarction, stroke, or peripheral vascular disease) with an LDL greater than or equal to 100 mg/dl ; Individuals with Diabetes (between the ages of 40-75) with an LDL greater than or equal to 100 mg/dl; Individuals without clinical ASCVD or diabetes with LDLC with an LDL greater than or equal to 100 mg/dl and estimated 10-year ASCVD risk 7.5%; Individuals without clinical ASCVD or diabetes with LDL cholesterol 190 mg/dl A prescription filled for a statin medication within the last 12 months (derived from pharmacy records or EHR); Imperfect statin adherence level as defined by one of the following: Medication Possession Ratio (MPR) less than or equal to 80% A score 0 on the 8-item Morisky Medication Adherence Questionnaire completed during enrollment

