be valued at appropriate wage rates. Long-term Effects of LDL Reductions on CVD Events and Cost-Effectiveness: The goal of lowering LDL is to prevent CVD complications. To estimate the cost and effectiveness associated with preventing cardiac outcomes, if our primary analyses of effectiveness indicate significant effects of the intervention, we will use a validated model of long-term cardiac risk, the Coronary Heart Disease (CHD) Policy Model. The CHD Policy Model is a computer-simulation, state-transition (Markov cohort) model of the incidence and prevalence of CVD (myocardial infarction, sudden death, revascularization, angina, stroke) and of the mortality and costs associated with these conditions in U.S. adults. The Model has been used to describe trends in CVD, project the effects of interventions to reduce CVD risk, and model the cost-effectiveness of interventions. [name], who leads the core modeling team, will adapt the Model to our study population, individuals with diabetes and/or known CVD. Based on decreases in LDL observed in the arms of this study, the Model will estimate the number and type of CVD events avoided, the quality-adjusted life years (QALYs) gained, and CVD treatment costs in each arm. We will use these estimates to calculate the cost-effectiveness of the intervention in each arm. Costs and health effects will be discounted 3% per annum. Return on investment: In addition to the cost-effectiveness analysis, if our primary analyses of effectiveness indicate significant effects of the intervention, we will conduct an analysis of potential return on investment for employers, the business case for preventing expensive health complications in the short- to medium-term. Using the CHD Policy Model we will estimate costs and savings of an incentives plan to the employer 3, 5, and 7 years after implementation. Savings will include reduced medical expenditures due to avoided CVD events and complications as well as increases in projected productivity as a result of reductions in CVD disability and death. Cost-effectiveness References 1. Peter J. Neumann, Gillian D. Sanders, Louise B. Russell, Joanna E. Siegel, Theodore G. Ganiats, editors, Cost-Effectiveness in Health and Medicine, second edition, New York: Oxford University Press, 2016. 2. Bibbins-Domingo K, Coxson P, Pletcher MJ, Lightwood J, Goldman L. Adolescent overweight and future adult coronary heart disease. *N Engl J Med* 2007;357:2371-9. 3. Odden MC, Coxson PG, Moran A, Lightwood JM, Goldman L, Bibbins-Domingo K. The impact of the aging population on coronary heart disease in the United States. *Am J Med* 2011;124:827-33 e5. 4. Lazar LD, Pletcher MJ, Coxson PG, Bibbins-Domingo K, Goldman L. Cost-effectiveness of statin therapy for primary prevention in a low-cost statin era. *Circulation* 2011;124:146-53. 5. Pletcher MJ, Lazar L, Bibbins-Domingo K, et al. Comparing impact and cost-effectiveness of primary prevention strategies for lipid-lowering. *Ann Intern Med* 2009;150:243-54. 6. Lightwood J, Bibbins-Domingo K, Coxson P, Wang YC, Williams L, Goldman L. Forecasting the future economic burden of current adolescent overweight: an estimate of the coronary heart disease policy model. *Am J Public Health* 2009;99:2230-7.

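### The long-term economic model is specified for a narrower population than the trial enrols, and it runs only after a significant LDL result although Aim 4 has no such condition

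*Combined protocol and SAP*

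**What the plan says.** Aim 4 (protocol, Overall objectives) is stated for every arm and without a condition: "Assess the cost-effectiveness of each of the interventions".

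The Analysis Plan then describes two layers of economic work.

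- **Within trial, unconditional.** "We will complete a within-trial analysis comparing incremental costs and incremental change in LDL in each arm, compared with control", over the 12 months, from a payer and then a societal perspective. Sensitivity analyses are planned and name the standard error of the effectiveness estimate as one source of uncertainty.
- **Long term, conditional.** The CHD Policy Model is to be used only "if our primary analyses of effectiveness indicate significant effects of the intervention". The input is described as "Based on decreases in LDL observed in the arms of this study", and the outputs are CVD events avoided, QALYs and treatment costs by arm. The employer analysis carries the same condition: "if our primary analyses of effectiveness indicate significant effects of the intervention, we will conduct an analysis of potential return on investment for employers". It is presented as additional to the cost-effectiveness analysis.

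On whom the model represents, the Analysis Plan says the modelling team "will adapt the Model to our study population, individuals with diabetes and/or known CVD". Key inclusion criteria also admit people with neither condition, through a 10-year ASCVD risk criterion of 7.5% with LDL of at least 100 mg/dl, or through a further route: "Individuals without clinical ASCVD or diabetes with LDL cholesterol 190 mg/dl".

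The SAP has no economic section, so it neither repeats nor clarifies any of this.

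**The concern.** There are two separate problems.

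**Population.** A long-term state-transition model turns an LDL difference into events through the baseline event rate of the people it represents. If it represents only people with diabetes or CVD while the trial also enrols others, the events, QALYs and costs do not describe the trial population.

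**Condition.** Non-significance is not evidence of no effect. A confidence interval that crosses zero can still include an LDL reduction worth paying for, and a decision-maker would then have no QALY or event estimate. The wording refers to the intervention in the singular, but there are three incentive arms. Whether one significant arm opens the model to all three, or each arm must qualify by itself, is left to be decided once results are known. In addition, when results are modelled only after they pass a significance threshold, the modelled effects are on average larger than the true ones.

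**Working it through.** **Population**

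| Eligibility route (Key inclusion criteria) | Inside the stated model population? |
|---|---|
| Clinical ASCVD, LDL at least 100 | Yes |
| Diabetes, age 40-75, LDL at least 100 | Yes |
| Neither condition, LDL at least 100, 10-year risk criterion 7.5% | No |
| Neither condition, LDL criterion 190 | No |

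The model's description matches the Target population section, which still speaks of diabetes and/or CVD. The Design section says the criteria were being changed, so the model text was probably not updated.

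Why this matters: the Power and Sample Size text takes a 10 mg/dl reduction to lower CVD events by about 5%. Events avoided per person are then roughly 0.05 × baseline risk, so an error in baseline risk carries through proportionally. If a share p of participants has k times the baseline risk of the diabetes/CVD group, the modelled events avoided are off by a factor of 1/(1 − p + pk). Neither p nor k is in the documents, so no figure can be given.

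**Condition**

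Inputs, from Power and Sample Size: 160 evaluable per arm, SD 28 mg/dl, two-sided alpha 0.05/3, design difference 10 mg/dl, dropout 14.5%. The SAP (section 2.1) uses Holm-Bonferroni.

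Reproducing the plan's figures:

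- 160/(1 − 0.145) = 187.1, and 4 × 187 = 748. Agrees.
- SE = 28 × √(2/160) = 3.13 mg/dl. The critical value is 2.394, so the smallest significant difference is 2.394 × 3.13 = 7.49 mg/dl.
- Power at 10 mg/dl = Φ(10/3.13 − 2.394) = Φ(0.80) = 78.8% per comparison, close to the stated 80%.

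Mean estimate in an arm that is itself significant (Bonferroni), for true effect d: E = d + SE × φ(z)/power, with z = 2.394 − d/SE.

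- d = 10: z = −0.80; 10 + 3.13 × 0.290/0.788 = 11.15
- d = 5: z = 0.80; 5 + 3.13 × 0.290/0.213 = 9.27

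The Holm and any-arm figures and the chance of no run come from a simulation of 1,000,000 trials with three arms sharing one control. All three arms have the same true effect. Ratios to the truth are in brackets.

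| True effect (mg/dl) | Power per arm (Bonferroni) | Mean estimate, per-arm rule, Bonferroni | Mean estimate, per-arm rule, Holm | Mean estimate, any-arm rule | No arm significantly better, model not run |
|---|---|---|---|---|---|
| 10 | 78.8% | 11.15 (1.12) | 10.8 (1.08) | 10.28 (1.03) | 5.5% |
| 7.5 | 50% | 9.99 (1.33) | 9.6 (1.28) | 8.51 (1.13) | 25% |
| 5 | 21% | 9.27 (1.85) | 8.9 (1.79) | 7.25 (1.45) | 59% |
| 2.5 | 5.5% | 8.82 (3.5) | 8.6 (3.4) | 6.3 (2.5) | 87% |

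With true effects of 10, 15 and 20 mg/dl, the any-arm rule gives means of 9.99, 15.00 and 20.00: no inflation. Rows below 10 mg/dl are assumptions shown as a range.

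**The case against.** The case for leaving the plan alone has real content.

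- **Aim 4 does not mention QALYs or a lifetime horizon.** The within-trial comparison covers every arm whatever the p-value. This stands: a reader might infer that a null trial leaves cost-effectiveness unanswered, and the documents do not support that. Only the long-term part is lost. Since return on investment is described as additional, its loss is not clearly a gap in Aim 4.
- **Removing the condition does not alter the input in a trial that passes it.** This also stands. The upward bias is an average over repeated trials. A reader might infer that any modelled result must be exaggerated, which does not follow.
- **The inflation depends on an undefined rule.** It is smaller under Holm or an any-arm rule. The primary model's adjustment for baseline LDL, ignored above, should reduce the SE and so the inflation. This limits the size but not the direction.
- **Uncertainty in the effect is already to be explored.** That is stated in the within-trial text and not for the long-term model. Varying an estimate by its standard error does not remove selection.
- **The population phrase may be stale wording, and the team may use the enrolled mix anyway.** Possibly. The text nonetheless describes the study population in terms that the inclusion criteria contradict, and the SAP is silent.

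**Conclusion.** Both problems hold, within limits.

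The population mismatch is a plain contradiction between the Analysis Plan and Key inclusion criteria. Following the model description as written would give participants without ASCVD or diabetes the wrong baseline risk. Its effect on QALYs and events cannot be sized from the documents.

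The significance condition leaves the long-term part of Aim 4 without an analysis after a null result. At the design effect this is a modest risk: about 5.5% of trials unmodelled, and an average input inflation of 3% (any-arm rule) to 12% (per-arm Bonferroni rule). It becomes material if true effects are well below plan: at an assumed 5 mg/dl in all arms, 59% unmodelled and 45% to 85% inflation. These figures assume 160 per arm, SD 28, a common true effect across arms, no baseline adjustment and no multiple imputation. They concern the difference from control.

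Neither problem touches the primary LDL inference or the within-trial economic comparison. A reader might conclude that the economic answer will be either missing or optimistic. That is too strong, because the within-trial analysis is unconditional and the inflation is small at the planned effect.

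**What to change.** 1. In the Analysis Plan, describe the model population as the enrolled mix, including participants without ASCVD or diabetes, and reconcile that text with Key inclusion criteria. The SAP already tabulates health condition and splits participants by ASCVD status, which helps to define the mix.
2. Remove the significance condition from the long-term cost-effectiveness model. Run it for each incentive arm against control, using the estimated LDL difference with its full uncertainty, for example by probabilistic sensitivity analysis with an acceptability curve. This extends to the long-term model the attention to the standard error already planned within trial.
3. Return on investment may stay conditional as an additional analysis, provided the text states whether one arm or each arm must be significant.

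The cost is protocol wording and extra runs by a modelling team already engaged, including runs when effects are small. Trial procedures, sample size and the primary test are unaffected.
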